**Figure 1 F1:**
[figure not shown]
An overview of the clinical assessment pathways for liver fibrosis in primary care. ALP, alkaline phosphatase; ALT, alanine aminotransferase; AST, aspartate aminotransferase; AUDIT, Alcohol Use Disorders Identification Tool; ELF, enhanced liver fibrosis test; GGT, gamma glutamyl transferase; LSM, liver stiffness measurement; T2DM, type 2 diabetes; VTCE, vibration controlled transient elastography.

Irrespective of which pathway a patient is recruited into, individuals with suspected moderate or advanced liver fibrosis (LSM>8 kPa), will be reviewed in secondary care to confirm their stage of liver fibrosis and institute specific treatment and/or enhanced lifestyle management depending on the underlying diagnosis within routine NHS clinical services.^30 31^ When cirrhosis is identified, patients will be entered into liver cancer and varices surveillance programmes according to current standard of care.^32^

These pathways will allow us to evaluate the diagnostic accuracy of FIB-4, ELF, PRO-C3, VCTE and novel biomarkers alone or in combination for advanced fibrosis/cirrhosis in individuals with risk factors for liver disease. Unique to this study, participants will also be followed longitudinally via their electronic health records and NHS Digital to assess long-term clinical outcomes.

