### Study outcomes

#### Primary outcome

The primary outcome of SOLID is to assess the number of patients identified with advanced liver fibrosis/cirrhosis using each of the pathways based on an overall clinical evaluation by a panel of hepatologists.

The presence of advanced fibrosis will be determined by an overall clinical assessment after secondary care review and will include all investigations undertaken in primary and secondary care. Where there is uncertainty about the stage of liver fibrosis, a liver biopsy will be offered as per usual clinical care. The overall clinical assessment for advanced fibrosis will be undertaken by three hepatologists. Where cases are equivocal, all the clinical data for these patients will be reviewed independently by each of the hepatologists to determine the presence of advanced fibrosis. An agreement analysis will be conducted to determine the concordance between hepatologists. Discrepancies will be resolved by consensus.

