#### Sample size calculation and power estimates

This study will recruit 3000 participants from Primary Care Networks in Northeast England. Searches in two practices indicate that at least 2600 of 20 000 patients meet the eligibility criteria and attend annual year of care reviews. In addition, approximately 200 patients attend 5-yearly health reviews. Approximately 1500 patients will be recruited into each pathway. We estimate that the prevalence of moderate/advanced fibrosis in the recruited population will be 5%–7.5%.^9 39 40^

With a prevalence of advanced fibrosis of 5%–7.5%, this will give us 150–225 true positives and 2775–2850 true negatives. The large sample of true negatives will result in higher precision to estimate specificity than sensitivity. The total sample size of 3000 will provide a precise estimate of the true prevalence for this population. If the true prevalence is 5%–7.5%, the expected width of the 95% CI for the population prevalence is 0.06–0.019.

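### The sample size section attaches one prevalence range, 5%–7.5%, to moderate/advanced fibrosis and then to advanced fibrosis, so the expected count of 150–225 endpoint cases is not secured

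*Protocol article*

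**What the plan says.** All of the planning figures are in the protocol article, *Sample size calculation and power estimates*. The target is given as "This study will recruit 3000 participants from Primary Care Networks in Northeast England", and "Approximately 1500 patients will be recruited into each pathway". The prevalence input reads "We estimate that the prevalence of moderate/advanced fibrosis in the recruited population will be 5%–7.5" per cent, and this is the sentence that carries the three citations. The following sentence reads "With a prevalence of advanced fibrosis of 5%–7.5%, this will give us 150–225 true positives and 2775–2850 true negatives".

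The condition of interest is set in *Primary outcome*: to "assess the number of patients identified with advanced liver fibrosis/cirrhosis using each of the pathways", as judged by a panel of hepatologists. *Assessment of the performance of the biomarkers* likewise takes advanced fibrosis as the target of the ROC analysis.

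The wider category appears under *Study design*, in the text with Figure 1: "individuals with suspected moderate or advanced liver fibrosis (LSM>8 kPa), will be reviewed in secondary care". The abstract and *Study procedures* describe LSM>8 kPa in similar terms, as significant/advanced and as moderate to advanced.

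**The concern.** The two adjacent sentences use the same numbers for two conditions that the protocol keeps apart. Moderate/advanced fibrosis is what a raised LSM suggests and what triggers referral. Advanced fibrosis/cirrhosis is what the hepatologists decide afterwards, and it is the endpoint. The *Introduction* supports the distinction: it uses 8 kPa to rule advanced disease out, and gives 12 kPa as the cut-off with 88% specificity for it. Advanced fibrosis is therefore a subset of moderate/advanced fibrosis, and the two can share a prevalence only if there are no moderate cases.

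The number of participants with the endpoint drives the precision of sensitivity, of the area under the ROC curve and of any other measure estimated among cases. The section itself names sensitivity as the less precisely estimated quantity. The same cases must also serve the analyses by suspected aetiology and the modelling of pathways. If the count rests on the wrong condition, the reader has no reliable view of what the study can deliver on its weaker side.

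**Working it through.** **Inputs from the article.** N = 3000, about 1500 per pathway, prevalence p = 5% to 7.5% (*Sample size calculation and power estimates*).

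**Assumptions, not in the article.** The share f of moderate/advanced cases that are advanced is taken as 75%, 50% or 25%. Sensitivity is taken as 80%. Specificity is taken as 88%.

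**1. Reproducing the plan's counts.** Cases = N × p: 3000 × 0.05 = 150 and 3000 × 0.075 = 225. Non-cases = N × (1 − p): 3000 × 0.95 = 2850 and 3000 × 0.925 = 2775. All four figures reproduce exactly. The range cited for moderate/advanced fibrosis was thus carried over unchanged to advanced fibrosis.

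**2. Counts if the cited label is right.** Advanced cases = N × p × f, for example 3000 × 0.05 × 0.50 = 75.

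**3. Half-width for sensitivity.** 1.96 × √(0.80 × 0.20 / cases) = 0.784 / √cases. For example, 0.784 / √150 = 0.064 and 0.784 / √75 = 0.091.

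**4. Width of the prevalence interval.** 2 × 1.96 × √(q(1 − q)/3000), where q = p × f.

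| Share advanced | Prevalence of advanced | Cases in 3000 | Cases per pathway | Half-width for sensitivity, all 3000 | Width of prevalence CI |
|---|---|---|---|---|---|
| 100% (as the counts imply) | 5%–7.5% | 150–225 | 75–113 | ±6.4 to ±5.2 points | 0.0156–0.0189 |
| 75% | 3.75%–5.6% | 113–169 | 56–84 | ±7.4 to ±6.0 | 0.0136–0.0165 |
| 50% | 2.5%–3.75% | 75–113 | 38–56 | ±9.1 to ±7.4 | 0.0112–0.0136 |
| 25% | 1.25%–1.9% | 38–56 | 19–28 | ±12.8 to ±10.5 | 0.0080–0.0097 |

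**5. Specificity.** 1.96 × √(0.88 × 0.12 / non-cases) is about ±1.2 points in every row, because non-cases only rise from 2775–2850 to at most about 2963.

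**Side note.** The article prints the width of the prevalence interval as 0.06–0.019. The upper figure agrees with 0.0189. The lower does not agree with 0.0156 and looks like a misprint of 0.016. This is separate from the label, but the same line has to be revisited.

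**The case against.** The strongest reply is that the direction of the error is not established. The cited sources are not at hand. If they report 5%–7.5% for advanced fibrosis, the slip is in the cited sentence, and 150–225 is correct. This stands. A reader might infer that the plan certainly overstates its cases, but the article supports that only conditionally. That the citations sit on the moderate/advanced sentence favours that label without proving it.

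A reader might also infer that a printed accuracy figure is false. None is. The section gives no numerical precision for sensitivity or specificity, only the statement that specificity will be the more precise, which remains true with fewer cases.

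A third tempting step is to set one pathway at a 50% share (38–56 cases, about ±13 to ±10 points) against the whole cohort with no reduction (150–225 cases, ±6 to ±5). That merges two separate halvings, and only one comes from the label. Within one pathway, the fair comparator is 75–113 cases, about ±9 to ±7.

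It is also fair to say that the shares are assumed, that at 75% the change is modest, and that 3000 is not derived from a required case count or a target precision. The primary outcome is to be described, with no power claim resting on 150–225. Finally, the terms *true positives* and *true negatives* plainly mean participants with and without disease. That is loose wording, and no calculation depends on it.

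None of this reconciles the two sentences. Nor is it detail that an article may leave to a fuller document: the conflict is between figures that are printed.

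**Conclusion.** The point holds in conditional form. One prevalence range is assigned to two conditions that the protocol treats as different, and the expected number of endpoint cases depends on which label is right. The multiplication is correct, so the fault lies in the definition of the input.

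If the range describes moderate/advanced fibrosis, then 150–225 is too high for the endpoint by a factor that the article does not allow one to fix. Under assumed advanced shares from 75% down to 25%, the count falls to between 113–169 and 38–56. At an assumed sensitivity of 80%, the half-width over all 3000 participants widens from ±5–6 points to between ±6–7 and ±10–13. The prevalence range behind the stated interval width would also belong to the wrong condition. Specificity is practically unchanged. If the range describes advanced fibrosis, only the cited sentence needs correcting. Either way, one of the two sentences must be changed, and only the sponsor can say which.

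**What to change.** State in *Sample size calculation and power estimates* which condition 5%–7.5% describes, in line with the cited sources.

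- If it is advanced fibrosis, correct the label in the cited sentence. The counts stay.
- If it is moderate/advanced fibrosis, keep it under that label and add a separate, sourced prevalence for advanced fibrosis/cirrhosis. From that, recompute the expected cases overall and per pathway and the width of the prevalence interval, and give the half-width for sensitivity at the expected number of cases.

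In both cases, relabel the counts as participants with and without advanced fibrosis, and check the lower figure of the printed interval width.

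The cost is a few lines of text and a short recalculation. Recruitment is unchanged. The one drawback is that the stated planning figures may become less favourable.

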## Methods and analysis

### Study design

SOLID is a prospective, observational cohort study where individuals with risk factors for fatty liver disease will have a liver health check to identify advanced liver fibrosis/cirrhosis when they attend their primary care annual chronic disease review. The diagnostic performance of fibrosis biomarkers for advanced fibrosis/cirrhosis with respect to long-term outcomes will be evaluated.

Primary care annual chronic disease reviews offer an ideal place to conduct a liver risk assessment since much of the information needed for this is already collected. Liver risk factors will be assessed, and individuals with obesity (BMI>30 kg/m^2^), T2DM or hazardous alcohol consumption (using Alcohol Use Disorders Identification Tool; (AUDIT score>8)) will have a ‘liver health check’ using established fibrosis biomarkers including FIB-4, ELF and VCTE. Blood samples will be taken for novel biomarkers, including PRO-C3, to evaluate their performance. Two pathways will be evaluated (figure 1): (1) all patients have FIB-4, ELF test and VCTE performed, and (2) patients have an initial assessment with the FIB-4 and ELF test, followed by VCTE in only those with increased FIB-4 and/or ELF.

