### Study procedures

All participants will have a liver fibrosis assessment using established biomarkers (VCTE and/or FIB-4 and ELF), blood tests and relevant clinical and demographic data collected at the time of assessment, as shown in table 1.

The optimum clinical pathway for the evaluation of liver fibrosis is not known so we plan to evaluate two pathways (figure 1) to determine which is most clinically and cost-effective. In pathway one, all patients will be offered VCTE and have blood tests for liver fibrosis biomarkers. In pathway two, patients with FIB-4>1.3 and/or ELF>9.8 indicating possible advanced fibrosis/cirrhosis will have VCTE to stage fibrosis.

VCTE will be conducted by trained operators at Newcastle Hospitals or in the primary care centre depending on the proximity of primary care sites to the hospital (sites close to the hospital will have VCTE performed at the hospital and those further away will have it performed at the practice). LSMs and controlled attenuation parameter readings will be obtained using a Fibroscan 430 mini+machine with M or XL probe as per the manufacturer’s recommendations. VCTE reading will be considered ‘reliable’ if they meet the accepted quality criteria of at least 10 readings from the same location with a single probe and the IQR/median ratio is less than 30% when the LSM exceeds 7.1 kPa.^35^

Individuals will be given a report of their liver assessment (LSM or FIB-4/ELF) to indicate their stage of liver fibrosis. All participants will be given relevant lifestyle advice and an information booklet entitled ‘Looking after your Liver’ (online supplemental file 1).

10.1136/bmjgast-2022-001092.supp1Supplementary data

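### The precision stated for true prevalence counts all 3000 participants as ascertained, but blood-negative participants in pathway 2 (about 1500 recruited) are never verified

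*Protocol article*

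**What the plan says.** All of the precision statements are in the protocol article under Sample size calculation and power estimates. The assumed prevalence is given as "We estimate that the prevalence of moderate/advanced fibrosis in the recruited population will be 5%–7.5" (per cent). The next paragraph applies the same range to advanced fibrosis and concludes that "this will give us 150–225 true positives and 2775–2850 true negatives", which is 5%–7.5% of 3000 and the remainder. It then states "The total sample size of 3000 will provide a precise estimate of the true prevalence for this population" and that "the expected width of the 95% CI for the population prevalence is 0.06–0.019".

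The same section says "Approximately 1500 patients will be recruited into each pathway". The two pathways do not ascertain disease in the same way:

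- **Pathway 1** (Study procedures): "In pathway one, all patients will be offered VCTE and have blood tests for liver fibrosis biomarkers".
- **Pathway 2** (Study design): "patients have an initial assessment with the FIB-4 and ELF test, followed by VCTE in only those with increased FIB-4 and/or ELF". Study procedures gives the thresholds: "patients with FIB-4>1.3 and/or ELF>9.8 indicating possible advanced fibrosis/cirrhosis will have VCTE to stage fibrosis".

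Study procedures also says that pathway 2 participants with low blood results stay in primary care, on the ground that such results rule out advanced fibrosis. Under Primary outcome, the reference standard is an overall clinical assessment made after secondary care review.

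**The concern.** A pathway 2 participant who has advanced fibrosis but low FIB-4 and ELF has no route in the study to VCTE or to the clinical assessment, and so counts as free of disease. Pathway 2 therefore measures cases detected by the triage. That equals prevalence only if the triage misses nobody whom pathway 1 would have found.

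The sample size section needs that zero miss rate, yet the Abstract says that the performance of these tests in primary care is not known, and estimating it is a reason for the study. Long-term follow-up through records captures clinical events and does not recover fibrosis status at baseline.

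At stake is a published precision that the design does not deliver, and the risk that a mixture of prevalence and yield is reported as true prevalence with an interval centred too low. The expected numbers of diseased and disease-free participants, which also underlie the remark on precision for sensitivity and specificity, rest on the same assumption.

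**Working it through.** **Inputs from the protocol article.** N = 3000, about 1500 per pathway, prevalence p of 5% to 7.5%, 95% confidence, printed widths 0.06 and 0.019. The triage sensitivity s, relative to the pathway 1 work-up, is not given and is varied here as an assumption.

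**1. Reproducing the plan's figures.** Full width = 2 × 1.96 × √(p(1−p)/n).

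- n = 3000, p = 0.075: 2 × 1.96 × √(0.075 × 0.925/3000) = 0.0189. The printed 0.019 reproduces.
- n = 3000, p = 0.05: 2 × 1.96 × √(0.05 × 0.95/3000) = 0.0156. The printed 0.06 does not reproduce. Wilson gives 0.0156 and the exact interval 0.0159. A width of 0.06 at 5% would correspond to n of about 203. It looks like a misprint of 0.016.
- 3000 × 0.05 = 150 and 3000 × 0.075 = 225, with remainders 2850 and 2775. These match.

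The calculation therefore treated all 3000 as fully ascertained.

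**2. Pathway 1 only, n = 1500.**

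- p = 0.05: 2 × 1.96 × √(0.05 × 0.95/1500) = 0.0221, with 75 expected cases.
- p = 0.075: 2 × 1.96 × √(0.075 × 0.925/1500) = 0.0267, with 112.5 expected cases.

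Both widths are √2 = 1.41 times those at n = 3000.

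**3. Simple pooling of both pathways.** Pathway 1 is taken here as fully ascertained and prevalence as equal in both pathways. Pathway 1 then has expectation p and pathway 2 has ps. With equal sizes the pooled expectation is m = p(1+s)/2, which is low by p(1−s)/2. The standard error is √{[p(1−p) + ps(1−ps)]/(4 × 1500)} and the nominal half-width is h = 1.96 × √(m(1−m)/3000). Coverage is Φ((p−m+h)/SE) − Φ((p−m−h)/SE).

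| s (assumed) | Pooled expectation at p = 5% / 7.5% | Coverage of nominal 95% CI at 5% / 7.5% |
|---|---|---|
| 1.00 | 5.00% / 7.50% | 95% / 95% |
| 0.95 | 4.88% / 7.31% | 94% / 93% |
| 0.90 | 4.75% / 7.13% | 90% / 87% |
| 0.80 | 4.50% / 6.75% | 74% / 63% |
| 0.75 | 4.38% / 6.56% | 61% / 45% |
| 0.60 | 4.00% / 6.00% | 20% / 7% |

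Example, p = 0.075 and s = 0.75: m = 0.0656, p−m = 0.0094, SE = 0.0045, h = 0.0089, so coverage is 0.455.

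**4. A corrected estimator.** Take blood-positive cases from both pathways (expected proportion a = ps, n = 3000) and blood-negative cases from pathway 1 only (b = p(1−s), n = 1500). The variance of the sum is a(1−a)/3000 + b(1−b)/1500 − 2ab/3000. Widths at 5%/7.5% are 0.0160/0.0194 at s = 0.95, 0.0171/0.0208 at s = 0.80 and 0.0185/0.0225 at s = 0.60. All lie between the n = 3000 and n = 1500 values.

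**The case against.** The strongest reply is that prevalence is not a listed outcome. The primary outcome is the number of patients identified by each pathway, which is detected yield, and no analysis in the article pools the pathways to estimate prevalence. This stands. A reader might infer that the primary analysis is biased, and the documents do not support that. The error is in a stated precision, and the bias arises only if the simple pooled proportion is used.

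Secondly, s is unknown. Referral on either raised test favours a high s, and the article says that both tests reliably exclude advanced fibrosis. At s = 0.95 the shortfall is only 0.13–0.19 percentage points. This also stands, so serious under-coverage cannot be claimed as a fact. But the article cannot take s = 1 either, since it treats test performance in this setting as an open question.

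Thirdly, pathway 1 is not fully verified. VCTE is offered, about 5% of measurements fail and fall back on FIB-4 and ELF, and participants below 8 kPa have no secondary care review. This qualifies the remedy and does not rescue the claim for 3000.

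Fourthly, using n = 1500 discards information from blood-positive participants in pathway 2. That is right, and 0.022–0.027 is the conservative end. The narrower alternative needs equal prevalence in the two pathways, and the article describes no randomisation between them.

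Finally, a reader might say that the printed interval is too narrow throughout. It is not: the printed 0.06 at 5% exceeds even the n = 1500 width. The comparison applies to 0.019 and to the apparently intended 0.016.

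**Conclusion.** The point holds as a flaw in the precision justification. That 3000 participants give the stated precision for true prevalence is wrong as written, because the figure of 0.019 and the counts 150–225 and 2775–2850 require disease status to be known in blood-negative pathway 2 participants, who are not verified.

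On pathway 1 alone the width is about 0.022 at 5% and 0.027 at 7.5%, against 0.016 and 0.019, with about 75–113 cases. The direction of bias in a simple pooled estimate is downward for any s below 1, provided that the pathways have equal prevalence and pathway 1 is taken as the standard. Its size depends wholly on s: slight near 0.95, substantial at 0.75 or below. The printed 0.06 is a separate error that needs no assumption. Severity is moderate, since no listed outcome rests on the pooled figure.

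**What to change.** In the sample size section:

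1. Base the prevalence precision on pathway 1: expected 95% CI width about 0.022 at 5% and 0.027 at 7.5% (n = 1500). Alternatively, name an estimator that corrects for partial verification, such as the one in step 4 of the working, with its assumption of equal prevalence in both pathways and a width given over a range of s.
2. Report the pathway 2 result as cases detected per 100 assessed, not as prevalence.
3. Replace the true positive and true negative counts with expected participants with and without the condition. In pathway 1 these are about 75–113 and 1387–1425.
4. State that pathway 1 is also incompletely verified, for the three reasons given under the objection.
5. Correct the printed 0.06. If the n = 3000 figure is kept for any purpose, it is about 0.016 at 5%.

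The cost is a few restated figures and a sentence or two on analysis, with no extra patients. The downside is that the stated precision becomes less favourable.

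### The printed 95% CI width of 0.06 at 5% prevalence should be 0.016; this is probably a dropped digit, and the sample size is unaffected

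*Protocol article*

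**What the plan says.** The point lies in the protocol article, under the heading Sample size calculation and power estimates. The section gives the expected numbers of people with and without the condition: "this will give us 150–225 true positives and 2775–2850 true negatives". It then asserts that "The total sample size of 3000 will provide a precise estimate of the true prevalence for this population". The supporting figure follows, conditional on the assumed range ("If the true prevalence is 5%–7.5"%): "the expected width of the 95% CI for the population prevalence is 0.06–0.019". The section names no interval method and no denominator other than 3000 for this figure. It also mentions the split between pathways: "Approximately 1500 patients will be recruited into each pathway". No other section gives a different width.

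**The concern.** The two printed widths run the wrong way. For a fixed sample size, the width of an interval for a proportion grows with p(1−p), which increases from p=0.05 to p=0.075. The width at the lower prevalence must therefore be the smaller of the two, yet the text gives 0.06 for the lower end and 0.019 for the upper end.

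What is at stake is the reliability of a published planning figure. Taken literally, a width of 0.06 around a prevalence of 5% is an interval of about 2% to 8%, which sits badly beside the claim of precision in the preceding sentence. It is the only interval width that the section reports. Anyone who later compares achieved with planned precision, or borrows the figure for another study, would start from a wrong number.

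**Working it through.** **Inputs**, all from the sample size section:
- n = 3000.
- Prevalence p = 0.05 to 0.075.
- Confidence level 95%, so z = 1.96.
- Check of the denominator: 0.05 × 3000 = 150 and 0.075 × 3000 = 225, leaving 2850 and 2775. These are the printed counts, so the section works with 3000 throughout.

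**Formula** (normal approximation, full width): W = 2 × 1.96 × √(p(1−p)/n).

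**Step 1: reproduce the upper figure.** At p = 0.075: W = 3.92 × √(0.069375/3000) = 3.92 × 0.004809 = 0.0189. This rounds to the printed 0.019, so the printed figures are full widths at n = 3000.

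**Step 2: the lower figure.** At p = 0.05: W = 3.92 × √(0.0475/3000) = 3.92 × 0.003979 = 0.0156. The printed value is 0.06, and 0.06/0.0156 = 3.85.

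**Step 3: look for a reading that gives 0.06.**

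| Reading | Width at 5% | Width at 7.5% |
|---|---|---|
| Printed | 0.06 | 0.019 |
| Normal approximation, n=3000 | 0.0156 | 0.0189 |
| Wilson, n=3000 | 0.0156 | 0.0189 |
| Clopper-Pearson, n=3000 | 0.0159 | 0.0192 |
| Agresti-Coull, n=3000 | 0.0157 | 0.0189 |
| Jeffreys, n=3000 | 0.0156 | 0.0189 |
| Continuity-corrected, n=3000 | 0.0159 | 0.0192 |
| Half-width, n=3000 | 0.0078 | 0.0094 |
| 99% level, n=3000 | 0.0205 | 0.0248 |
| One pathway, n=1500 | 0.0221 | 0.0267 |

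None comes near 0.06 at 5%, and the readings that change the level, the denominator or the half-width convention also lose the match at 7.5%. Reversing the range (0.06 at 7.5%, 0.019 at 5%) fails at both ends, since the values there are 0.0189 and 0.0156.

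**Step 4: bounds.**
- The largest normal-approximation width at n = 3000 occurs at p = 0.5: 3.92 × √(0.25/3000) = 0.0358. So 0.06 cannot arise at any prevalence.
- The sample size that would give a width of 0.06 at 5% is n = 3.92² × 0.0475/0.06² = 15.3664 × 0.0475/0.0036 ≈ 203, far from 3000.

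**Step 5: the likely cause.** Inserting a single 1 turns 0.06 into 0.016, which is the correct value to three decimals under every 95% method in the table. A shifted decimal point (0.006) does not fit: that width at 5% would need about 20,274 participants.

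**The case against.** The strongest reply is that this is a misprint without consequence. One end of the range reproduces exactly, and one missing digit repairs the other. The error also understates the study's precision. The section does not derive 3000 from a target width: it describes how many eligible patients the practices hold, gives the expected case counts, and then reports the width that results. No design choice, analysis or expected count changes when the figure is corrected.

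All of that stands, and it limits how far the point can be taken. Three stronger readings are tempting, and the document supports none of them.

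- **That the precision claim or the sample size is undermined.** A reader who takes 0.06 literally might infer this. The corrected interval at 5% is about 4.2% to 5.8% (0.05 ± 0.0078), which supports the claim.
- **That the authors' calculation was wrong by a factor of almost four.** The ratio is real, but the match at 7.5% points to correct working and a printing slip.
- **That the width should be computed for pathway 1 alone (n=1500), as the fully verified group.** The section bases this figure explicitly on the total of 3000. Nor is pathway 1 fully verified. Everyone in it is offered elastography, but under Study procedures those with a stiffness below 8 kPa stay in primary care in either pathway. Under Primary outcome, advanced fibrosis is determined after secondary care review.

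What the reply does not do is make the printed number right. It is a definite quantitative statement in the section that describes the study's precision, and it should be correct.

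**Conclusion.** The point holds as a minor correction. With 3000 participants the expected full width of the 95% interval is 0.016 at 5% prevalence and 0.019 at 7.5%. The printed 0.06 is too large by a factor of about 3.8, and the printed ordering is impossible.

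The conclusion assumes a simple binomial proportion with all 3000 participants in the denominator, which the section's own case counts and the reproduced 0.019 both confirm. It does not depend on the choice of interval method, since every 95% method tried gives 0.0156 to 0.0159 at 5%. That the cause is a dropped digit is an inference, and the correction does not rest on it. The error calls for no change to the design, the sample size or the analysis.

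**What to change.** In the sample size section, replace the printed range of widths with 0.016–0.019. Naming the interval method in the same sentence would help, though all the usual methods agree to about three decimals. The cost is one corrected figure. Recruitment and the neighbouring sentences stay as they are.
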